# HYPofractionated Adjuvant RadioTherapy in 1 versus 2 weeks in high-risk patients with breast cancer (HYPART): a non-inferiority, open-label, phase III randomised trial

**DOI:** 10.1186/s13063-023-07851-7

**Published:** 2024-01-02

**Keywords:** Breast cancer, Radiotherapy, Hypofractionation, Acute toxicity, Late toxicity, Recurrence, Quality of life, Survival

## Abstract

**Background:**

Breast cancer is the most common cancer in women. Radiotherapy is an important part of breast cancer treatment after surgery. Breast cancer radiotherapy is usually delivered in 3–5 weeks. This is a long duration for women with breast cancer to stay away from the family and work. We wanted to reduce this duration so that the wages loss and the logistics can be minimised for these patients. Hypofractionation, i.e. high dose per fraction, is delivered in a smaller number of days. In this study, we will compare a 1-week schedule of hypofractionated adjuvant whole breast/chest wall and/or regional nodal radiotherapy against 2 weeks for locoregional disease control, toxicities, quality of life (QoL), survival and second cancers after primary surgery in patients with breast cancer.

**Methods:**

Eligible patients with breast cancer after mastectomy or breast conserving surgery (BCS) will be treated with a radiotherapy dose of 26 Gy in 5 fractions over 1 week in the study arm and 34 Gy in 10 fractions over 2 weeks in the control arm. The primary endpoint of this noninferiority study will be locoregional tumour control. Secondary endpoints will be early and late radiation toxicities, quality of life, contralateral primary tumours, regional and distant metastases, survival and second cancers. A total of 1018 patients will be randomised (1:1) to receive 1 week or 2 weeks of radiotherapy. An event-driven analysis will be performed after at least 94 patients have documented locoregional recurrences. Acute radiation toxicity will be assessed and scaled according to the RTOG grading system. Late radiation toxicity will be assessed with the Radiation Therapy Oncology Group and the European Organisation for Research and Treatment of Cancer late radiation morbidity scale. Cosmetic assessment will be done using Harvard/NSABP/RTOG breast cosmesis grading scale at baseline and 3 and 5 years. QoL will be assessed with EORTC QLQ-30 and EORTC QLQ-BR 23 at baseline and 3 and 5 years.

**Discussion:**

Hypofractionation reduces treatment time to half while maintaining breast cosmesis and gives control rates equal to conventional fractionation. This is possible because breast tissue can tolerate high dose per fraction. In this study, we presume that 1-week radiotherapy will be non-inferior to 2 week radiotherapy, i.e. disease control will be similar with both the schedules without additional side effects, and QoL of these patients will be maintained. If we are able to achieve these outcomes, then patients will be able to complete their radiotherapy in less duration. There is not much data on regional nodal irradiation with hypofraction in breast cancer. We have used hypofraction for regional nodal irradiation in the past and not encountered any safety issue. If we are able to prove that late-term effects are comparable in the two schedules, it will make the radiation oncologist confident about hypofractionation in breast cancer. As breast cancer is a leading cancer in females and radiation therapy is an integral part of its local management, hypofractionation will help radiation centres worldwide to meet the growing need for radiation treatment in breast cancer, particularly in developing countries where resources are limited. It will also reduce the financial burden on the patient and family. Since we will treat these patients with both simple and complex radiotherapy techniques, it will also be possible for the low-income countries to follow this trial without needing a high-end or expensive radiotherapy equipment as the planning and treatment process will be very simple.

**Trial registration:**

The trial is registered with ClinicalTrials.gov ID NCT04472845 and CTRI with REF/2020/09/037050.

**Supplementary Information:**

The online version contains supplementary material available at 10.1186/s13063-023-07851-7.

## Background

In the past, standard radiotherapy for breast cancer was 50 Gy of dose delivered in 25 fractions over 5 weeks. This is called conventional fractionation; here, dose per fraction is 2 Gy. Sometimes, in young patients and those with high-risk disease, this is followed by a boost dose of 10–20 Gy in 5–10 fractions delivered over 5–10 days, which increased this treatment duration to 6–7 weeks, which is a long time. Hypofractionation is high dose per fraction delivered in a smaller number of days. We at PGIMER, Chandigarh, India, have been practicing hypofractionated radiotherapy in breast cancer patients for the last 5 decades. Our standard doses have been 35 Gy/15#/3wks to the chest wall after mastectomy and 40 Gy/16#/3wks after breast conserving surgery (BCS). We have published our results with moderate hypofractionated radiotherapy (35–40 Gy delivered in 15 fractions over 3 weeks) in patients with breast cancer and observed comparable favourable clinical outcomes [1–6]. Hypofractionation is also a routine practice in the UK and in a few centres in Canada [7, 8]. A study from Beijing also reported similar outcomes with conventional and hypofractionated radiotherapy [9]. The current standard for hypofractionation in breast cancer is 40–42.5 Gy delivered in 15–16 fractions over 3 weeks followed by a boost of 10–16 Gy in 5–8 fractions delivered over 1–2 weeks [6]. This is also called moderate hypofraction. Moderate hypofractionation may not be the upper limit of hypofractionation in breast cancer because breast tissue has low α/β ratio of 3.5 [7]. The ratio α/β is the dose at which the linear and quadratic component of cell killing are equal. α damage leads to single strand break in DNA which might be repairable, whereas β damage leads to double strand DNA damage which is not repairable. β damage occurs at high dose per fraction. This is a concept of radiobiology where α/β is assumed to be 3 Gy for late-responding tissue and 10 Gy for early responding tissue. With α/β of 3.5 for the breast, it behaves like a late responding tissue, which means high dose per fraction (hypofraction) is more suitable to treat breast cancer. So, accelerated hypofractionation (34 Gy delivered in 10 fractions over 2 weeks) is also a possibility in breast cancer [10–13]. With this background, we think that it is possible to reduce this treatment duration further. A recent study has also shown that 1-week treatment is similar to 3-week treatment in patients with early breast cancer [14]. We have completed a trial where we compared a 3-week schedule to 2-week and observed similar acute toxicity but cosmetic outcome was better with 2-week schedule [15]. Therefore, we chose the 2 weeks schedule as a comparator arm.

In this study, we want to test a 1-week schedule of hypofractionated adjuvant whole breast/chest wall and/or regional nodal radiotherapy against 2 weeks for locoregional control, acute and late toxicities, QoL, survival and second cancers after primary surgery in patients with breast cancer.

## Methods/design

We used the SPIRIT reporting guidelines (Supplementary file) [16]. This study will be a randomised, non-inferiority, open-label, phase 3 trial, with patients to be recruited from a single institute. Other institutes will be invited if they are willing to participate. Patients to be included in this study will be pre-operatively staged according to American Joint Committee on Cancer (AJCC) 8th edition, International Union against cancer (which uses TNM staging), as stage III breast carcinoma. For patients who receive adjuvant chemotherapy, pathological stage will be reflected, and for those with neoadjuvant chemotherapy, the stage which is higher (clinical/pathological) will be reflected. A total of 1018 patients with histologically proven post lumpectomy/mastectomy cases of carcinoma breast suitable for radiotherapy will be enrolled in this study. Patients will be evaluated at the Department of Radiation Oncology Post Graduate Institute of Medical Education & Research, Chandigarh, India. A thorough clinical examination followed by routine investigations which will include hemogram, liver function tests, kidney function tests, mammography, chest X-ray, ultrasound of abdomen/CECT chest, abdomen and pelvis and whole-body bone scan. At first visit, the patient will be screened, and if she/he agrees, the written informed consent will be taken from all the patients by [name], residents/clinical associates. If the patient needs more time to think over the study, then the consent will be taken in the subsequent visit. Patients must meet all of the following inclusion criteria and none of the exclusion criteria:

Inclusion criteriaAge ≥ 18–75 yearsFemale or maleInvasive carcinoma of the breastBreast conserving surgery (BCS) with axillary clearance or total mastectomy with axillary clearance (TMAC) (reconstruction allowed but not with implant; tissue expanders with distant metal ports are allowed)Concurrent trastuzumab and hormone therapy is allowedAxillary staging and/or dissectionComplete microscopic excision of primary tumourpT3-4, pN2-3, M0 diseaseClinical stage III disease or pathological node positive if they have received neo-adjuvant chemotherapyWritten informed consentAble to comply with follow-up

Exclusion criteriaSupraclavicular node or internal mammary node or distant metastasisPast history of malignancy except (i) basal cell skin cancer and CIN cervix uteri or (ii) non-breast malignancy allowed if treated with curative intent and at least 5 years disease freeContralateral breast cancer, including DCIS, irrespective of date of diagnosisBreast reconstruction using implantsPregnancy (a sexually active fertile female needs to agree to use contraceptives)Concurrent cytotoxic chemotherapy (sequential neoadjuvant or adjuvant cytotoxic therapy allowed)

### Radiotherapy planning

For 2-dimensional (2D) planning, patients will be in supine position on a breast board with ipsilateral arm abducted to 90°. Patients will be planned using 2-D fluoroscopic conventional simulator with two tangential fields to breast/chest wall and a single incident field to supraclavicular fossa. Field marking for breast/chest wall will include midline medially, midaxillary fold laterally, 2nd intercostal space cranially and 1 cm below opposite inframammary fold caudally. For supraclavicular field, caudal border will be cranial border of breast/chest wall field, cranially thyroid notch, medially along medial border of sternocleidomastoid muscle and laterally insertion of deltoid. Central lung distance (CLD) will be recorded for all patients. Wedge of 30° will be used in patients with BCS.

For conformal techniques, a CT-based three-dimensional planning will be used to reconstruct radiotherapy target volume for treating breast/chest and locoregional lymph nodes. The patients will be positioned supine on a breast board with arm abducted above the head on arm rest in planning CT in radiotherapy department. CT axial cuts will be taken from the level of larynx to upper abdomen, including both the lungs with a scan thickness and index of 3 mm. CT images will be transferred to the treatment planning system (TPS). The chest wall or whole breast, heart, bilateral lungs and opposite breast will be contoured using Radiotherapy Oncology Group (RTOG) contouring guidelines. For left anterior descending (LAD) coronary artery contouring, the left coronary artery will be identified, and its course was followed. LAD will be contoured from the place where the it branches away from the main left coronary artery and then runs towards the front and down towards the heart apex. It will be divided in to proximal and distal parts. Distal LAD will be the part which lies very near to the chest wall towards the apex of the heart. No additional margin will be given to LAD. The treatment parameters, patients and OARs outlines will be exported to computerized TPS, and plans will be made using standard tangent fields.

Radiotherapy dose to chest wall, axilla level III and supraclavicular fossa will be of 26 Gy in 5 fractions over 1 week in the study arm and 34 Gy in 10 fractions over 2 weeks in the control arm. BCS patients will receive a sequential boost of 8 Gy/2#/2days or simultaneous integrated boost (SIB) to a total dose of 32 Gy in the study arm and 40 Gy in the control arm. Treatment will be done on a linear accelerator with 6 or 10 MV photon energy. Boost can be with photons or electrons. One-centimetre bolus will be used in all postmastectomy patients, daily in study arm and in 50% of treatment in the control arm. Dose will be prescribed at mid-separation in 2D technique and the dose covering 95% of the planning target volume with three-dimensional conformal (3D-CRT) or intensity-modulated radiotherapy (IMRT).

Supraclavicular fossa (SCF) and axilla level III will be treated in patients with T3-4 disease with lymphovascular invasion, grade 3 or N2 disease and T3-4 disease treated with neoadjuvant chemotherapy after adequate axillary dissection. Level I and II axilla will be irradiated in patients with inadequate axillary dissection (< 10 lymph nodes) and if there is extracapsular extension. The prescribed dose to the area will be defined as the dose to the point at 3 cm beneath the skin in two-dimensional radiotherapy technique or the dose covering 95% of the planning target volume with 3D-CRT or IMRT.

Internal mammary node (IMNs) radiation will be done in T3-4 central and inner quadrant lesions, patients with N2 disease and in patients having IMN on imaging. IMNs will be irradiated with a separate 12 × 5 cm single field. The first three intercostal spaces will be included in the IMN target volume. The medial border of the IMN field will be midline; lateral border 4 cm lateral to the midline; the superior border will abut the inferior border of the supraclavicular field; and the inferior border will be above the xiphoid. Dose will be 34 Gy/10#/2weeks in the control arm and 26 Gy/5#/1 week in the study arm. Dose will be prescribed at 3 cm depth. IMNs can be treated with electrons or photons with 2D/3D/IMRT techniques. Imaging will be done for set-up verification on alternate days in the study arm and once weekly in the control arm.

Hormonal therapy may be given to oestrogen receptor-positive or progesterone receptor-positive tumours and anti-HER2-targeted therapy (e.g. trastuzumab) for those with HER2-positive disease depending on the affordability.

### Assessment

Patients will be assessed for medical history, a physical examination and a blood test before radiotherapy, once per week during radiotherapy and 2 weeks after radiotherapy (Fig. 1). Patients will be followed up every 3 months for 2 years after radiotherapy, then every 6 months from 3 to 5 years, and yearly thereafter. Skin, subcutaneous toxicity and cosmetic assessment will be done before treatment and then in regular follow-up of the study. Acute radiation toxicity will be assessed and scaled according to the RTOG grading system (Table 1). Acute toxicity will be accessed weekly during radiotherapy, at the time of completion and at 1 month after completion of radiotherapy. Late radiation toxicity will be assessed with the Radiation Therapy Oncology Group and the European Organization for Research and Treatment of Cancer (EORTC) late radiation morbidity scale at 6 months, 1 year, 2 years, 3 years, and 5 years. Cosmetic assessment will be done using Harvard/NSABP/RTOG breast cosmesis grading scale at baseline and 3 and 5 years. QoL will be assessed with EORTC QLQ-30 and EORTC QLQ-BR 23 at baseline and 3 and 5 years. Any adverse event will be communicated to the IEC. Patients will be reminded for follow-up by scheduling appointments and monitoring. Missed patients will be contacted by telephone, mails and written letters.

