For the primary efficacy end point, we will use the cumulative incidence method to estimate the actual incidence of locoregional recurrence at different time points, with death without locoregional recurrence as a competing risk. We will use the log-rank test and Cox regression model for statistical inference based on cause-specific hazards. We will calculate overall survival and disease-free survival using the Kaplan-Meier method, and we will analyse these endpoints using the log rank test and Cox regression model. Acute and late toxicities will be summarised as frequency and severity on the basis of their association with protocol treatment; *χ*^2^ tests will be used to compare the differences. The primary endpoint and all efficacy endpoints will be analysed in a modified intention-to-treat population (i.e. including all eligible patients who will undergo randomisation but exclude those who are considered ineligible). On the basis of the study design, the primary endpoint locoregional recurrence will be analysed at a one-sided significance level of 0.05 and reported with a two-sided 90% CI. All other statistical tests will be two sided, and *p* values of < 0.05 will be taken as significant. All tests will be performed using SPSS (Statistical Package for the Social Sciences) v.23.0.

No interim analysis is planned. Any adverse outcome or toxicity from the radiation schedules will be reported to the IEC. Final decision to terminate the trial lies with the IEC. Patient confidentiality will be maintained, and re-identifiable-identifiers will be removed and replaced by a code.

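### Acute toxicity grading follows treatment length: the 1-week arm is graded one time fewer, and neither arm is graded for about 30 days after completion

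*Protocol article*

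**What the plan says.** The Assessment section of the protocol article gives one acute grading rule for both arms, on the RTOG scale: "Acute toxicity will be accessed weekly during radiotherapy, at the time of completion and at 1 month after completion of radiotherapy". The same section schedules a history, examination and blood test before treatment, and then "once per week during radiotherapy and 2 weeks after radiotherapy". The acute grading sentence does not list that 2-week visit. The section adds: "Skin, subcutaneous toxicity and cosmetic assessment will be done before treatment and then in regular follow-up of the study". Regular follow-up is every 3 months for the first 2 years.

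Radiotherapy planning sets the treatment length: "26 Gy in 5 fractions over 1 week in the study arm and 34 Gy in 10 fractions over 2 weeks in the control arm". Patients with breast conserving surgery also receive a boost, either integrated or given sequentially over 2 further days.

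For the analysis, Statistical considerations states: "Acute and late toxicities will be summarised as frequency and severity on the basis of their association with protocol treatment". The arms are compared by chi-square tests. The article does not say whether the worst grade over all gradings or the grade at each occasion is compared. The Outcomes section lists acute toxicity among the secondary endpoints.

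**The concern.** The number of acute gradings, and their timing from the first fraction, depend on the randomised arm. If toxicity is summarised as the worst grade or as ever having occurred, an additional grading can raise the recorded figure but never lower it. Two arms with the same true reactions could then be recorded differently.

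Separately, a reaction that appears and settles within the month after completion is not graded in either arm, even though patients attend a visit in that month.

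The conclusion at stake is stated in the Discussion paragraph of the abstract: that the shorter schedule gives similar disease control with no added side effects. Acute grades that were never collected cannot be recovered at the analysis stage, so this has to be settled in the visit schedule.

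**Working it through.** The article gives no figure for acute toxicity, so there is none to reproduce. The primary sample size (94 events, 1018 patients) does not enter.

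**Inputs from the article.** Grading weekly, at completion and 1 month after completion; a visit 2 weeks after radiotherapy (Assessment). Treatment of 5 fractions in 1 week versus 10 in 2 weeks; a sequential boost adds 2 days (Radiotherapy planning).

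**Assumptions.** Day 0 is the first fraction, on a Monday. Treatment is on weekdays without interruption. One month is 30 days. The last weekly grading is also the completion grading unless stated otherwise.

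**Step 1: count the gradings.**
- No sequential boost: study days 4 and 34 (2 gradings); control days 4, 11 and 41 (3).
- Sequential boost: study days 4, 8 and 38 (3); control days 4, 11, 15 and 45 (4).
- No sequential boost, last weekly and completion gradings held separately: 3 versus 4.

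The study arm has one fewer under each reading.

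**Step 2: gap after completion.** Study: 34 − 4 = 30 days. Control: 41 − 11 = 30 days. The gap is the same length in both arms.

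**Step 3: effect of the count alone.** Suppose the arms are identical and each grading independently records a given grade with probability q. The ever-recorded proportion is 1 − (1 − q)^k for k gradings.

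| q | k = 2 | k = 3 | difference |
|---|---|---|---|
| 0.2 | 36.0% | 48.8% | 12.8 points |
| 0.3 | 51.0% | 65.7% | 14.7 points |
| 0.4 | 64.0% | 78.4% | 14.4 points |

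For 3 versus 4 gradings at q = 0.2, the figures are 48.8% and 59.0%, a difference of 10.2 points. If gradings within a patient are fully correlated, both arms record q and the difference is zero. The values of q are assumed.

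**Step 4: effect of timing.** Suppose the reaction follows a bell-shaped course with SD w around its peak day p. The share of the peak seen at the best-placed grading day d is the maximum over d of exp(−½((d − p)/w)²). Peak day and shape are assumptions. For a peak counted from the first fraction, with w = 5 days and no sequential boost:

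| peak day | study | control |
|---|---|---|
| 10 | 0.49 | 0.98 |
| 14 | 0.14 | 0.84 |
| 18 | 0.02 | 0.38 |
| 28 | 0.49 | 0.03 |

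For example, at day 14 the study arm's nearest grading is day 4, giving exp(−½(10/5)²) = 0.14. The control arm's is day 11, giving exp(−½(3/5)²) = 0.84. The control schedule is better placed for peaks between (4 + 11)/2 = 7.5 and (11 + 34)/2 = 22.5 days. Just beyond that the study schedule is better placed, so the direction reverses.

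For a peak counted from the end of treatment, capture is equal: 0.38 in both arms at 7 days after completion, and 0.02 in both at 14 days.

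**Step 5: grading added at the 2-week visit.** Study days become 4, 18 and 34; control days become 4, 11, 25 and 41. The longest ungraded interval after completion falls from 30 to 30 − 14 = 16 days in both arms. For a peak at day 14 from the start (w = 5), capture becomes 0.73 versus 0.84. For a peak 14 days after completion it rises from 0.02 to 1.0 in both arms. The occasions common to both arms are then days 4, 18 and 34 versus 11, 25 and 41, which are 7 days apart when counted from the first fraction. For a peak at day 18 from the start, capture would be 1.0 versus 0.38, so a timing difference can remain and can run against the study arm.

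**The case against.** The strongest counter-argument is that unequal counts need not produce bias. Relative to completion, the control arm's extra grading falls at about fraction 5 of 10, or 17 of 34 Gy (5 × 3.4 Gy). If a patient's grade at completion is at least the mid-course grade, that extra grading adds nothing to the worst grade. If the arms are compared occasion by occasion, the count has no effect either, and the choice of summary commonly belongs to the analysis plan. All of this stands. It makes the bias a possibility with a range that includes zero.

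A reader might infer that the month without grading itself favours the new schedule. The article does not support that, because the rule is timed from completion and leaves the same 30 days in both arms. A reader might also take the comparison to be certainly biased towards the 1-week arm. The article gives no time course for the reaction, and Step 4 shows a tilt towards that arm, no difference, or a reversal, depending on the course assumed.

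Three other defences carry less weight. Blinded outcome assessors do not equalise the number or timing of gradings. Skin assessment at regular 3-monthly follow-up does not fall within the first month. The patient assessment figure (Fig. 1), which is not shown in the text available, may assign acute grading to the 2-week visit; if it does, the grading sentence in Assessment should be brought into line with it. An analysis plan can restrict the comparison to common occasions, but it cannot supply grades that were not collected.

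**Conclusion.** The point holds in a limited form. The schedule as written gives the 1-week arm one fewer acute grading, and it does not assign acute grading to a visit that already exists 2 weeks after radiotherapy.

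A worst-grade or ever-occurred comparison may be biased, plausibly towards the 1-week arm. The 13–15 points are an illustration under independent gradings with an assumed detection probability of 0.2–0.4 for 2 versus 3 gradings. They are not an estimate for this trial, and the effect of the count can be zero.

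The 30-day gap is not differential in itself. It can hide reactions in both arms, and that weakens a claim of no additional side effects. The point concerns a secondary endpoint and leaves the primary analysis and sample size untouched. It is worth correcting because the correction is cheap.

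**What to change.** 1. Add RTOG acute grading to the existing visit 2 weeks after radiotherapy, in both arms, and name that visit in the acute grading sentence of Assessment.
2. Base the between-arm comparison of worst grade and frequency on the occasions common to both arms: completion, 2 weeks after and 1 month after.
3. Report the control arm's extra on-treatment grade separately.
4. State when reporting that the common occasions fall about a week apart between arms when counted from the first fraction. The change equalises the number of gradings and their timing from completion, but not their timing from the start.

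The cost is one extra CRF page at a visit that already takes place. Recruitment began on 1 April 2021, so some patients will already be past that visit. They contribute only the completion and 1-month grades, and a comparison on those two occasions needs no new data.
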